### Objectives and hypotheses

The primary objective of this study is to evaluate the comparative long-term (one-year) effects of ERVs and portable HEPA air cleaners on reducing exposure to indoor particulate and gaseous pollutants and mold, as well as on improving asthma-related health outcomes in inner-city children and adults with asthma in the Dallas-Fort Worth (DFW) area of Texas. We hypothesize that year-long use of ERVs and portable HEPA air cleaners will lead to improvements in IAQ and asthma-related health outcomes during the post-intervention period compared to the pre-intervention period, whereas control groups are expected to show no significant changes. Further, we hypothesize that two interventions will differ in both the profiles and magnitudes of IAQ and health improvements, as ERVs are designed to reduce both particulate and gaseous pollutants and help control indoor humidity to lower the risk of mold growth, whereas HEPA air cleaners primarily remove airborne particles from indoor air.

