### Interventions

The AIRVAC study will involve ERV and HEPA air cleaner interventions aimed at improving IAQ and asthma-related health outcomes. Following the pre-intervention period, participants will be randomized to receive one of four interventions during the 1-year post-intervention period: (1) active ERV, (2) sham (placebo) ERV, (3) active portable HEPA air cleaner, or (4) sham (placebo) portable HEPA air cleaner.

Due to the specific housing conditions required for ERV installation, including accessible ductwork for supply and exhaust, adequate space and access for the ERV unit, electrical safety, and proper sealing of penetrations, a constrained randomization approach will be employed. Prior to randomization, each home will undergo an ERV installation feasibility assessment based on the information collected during the initial walk-through visit (V0). Homes that meet the ERV installation criteria will be eligible for assignment to ERV or portable air cleaner study arms, whereas homes that do not meet the ERV installation criteria will only be eligible for portable air cleaner study arms.

After intervention eligibility is determined, participants will be randomly assigned to the available active or sham groups using a computer-generated randomization sequence in Stata (v.19) [35]. Stratified randomization will be used to maintain balance across the four study arms within predefined strata based on key housing and participant characteristics. Housing characteristics will include building envelope air leakage measured by blower door testing, home size, and exhaust fans, while participant characteristics will include baseline health status. The randomization sequence will be generated and securely maintained by the PIs. Allocation assignments will remain concealed until completion of eligibility confirmation and baseline assessments. All participants will remain blinded to whether they receive the active or sham intervention throughout the entire study duration. To maintain participant blinding, all field research staff and HVAC contractors will be trained not to disclose intervention assignments to participants.

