For the 40 homes assigned to the ERV intervention, we will install a Broan-NuTone B160E75RS/T units. The required airflow rate of each unit will be determined based on the floor area and number of bedrooms, in accordance with ASHRAE Standard 62.2–2025, *Ventilation and Acceptable Indoor Air Quality in Residential Buildings* [36]. The building envelope leakage measured during the initial home assessments will be applied as infiltration credits in the ventilation rate calculations to account for natural air leakage. The ERV units will then operate continuously at the specified ventilation rate throughout the intervention period.

Sham ERVs will be installed in the same manner as active units but will be programmed to operate in recirculation mode, without supplying outdoor air or altering ventilation rates. They will draw indoor air from the home and return it without any dilution or exchange with outdoor air, as the outdoor air intake damper remains closed. Participants will not have access to the control panel settings during the study period. This modification will maintain participant blinding, as occupants will experience airflows and fan noise similar to those of active ERVs.

Forty (40) homes in the air cleaner group will receive a Medify Air MA-112 unit, primarily placed in the living room (or in the bedroom if occupants spend the majority of their time). In cases where additional eligible family members reside in the same household, an additional Medify Air MA-50 unit will be deployed in their bedrooms. Both air cleaners are equipped with HEPA and activated carbon filters. In homes assigned to the sham control group, filters will be removed from the air cleaner units. Both active and sham air cleaner units will be sealed and have identical external appearance and installation configurations to maintain participant blinding.

During scheduled home visits in the post-intervention period, field staff will check the ERV and air cleaner units to verify proper operation and confirm that blinding measures are maintained, including ensuring that ERV control panel settings remain unchanged and inaccessible to participants and that air cleaner unit seals remain intact.

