### Health outcome assessments

#### Primary outcome measures.

We will use the following measures to assess asthma control:

Asthma Control Test (ACT): Monthly ACT surveys will be administered electronically using an online survey link distributed to participants. The ACT is a 5-item, clinically validated questionnaire designed to assess the multi-dimensional nature of asthma control, including asthma symptoms, use of rescue medications, and the impact of asthma on daily functioning [38]. ACT scores range from 5 (“poor control of asthma”) to 25 (“complete control of asthma”), with a cut-off of 19 used to identify participants with suboptimal asthma control according to the Global Initiative for Asthma (GINA) guidelines: a score >19 indicates “well-controlled asthma,” whereas a score ≤19 indicates “poorly controlled asthma” [39,40]. Children under 12 years of age will complete the Childhood Asthma Control Test (C-ACT).Asthma Control Questionnaire (ACQ): In addition to monthly ACT, we will administer the ACQ during the home visits (V1-V4) to assess asthma control more comprehensively. The ACQ consists of 7 items covering asthma symptoms, rescue bronchodilator use, and lung function (FEV_1_, forced expiratory volume in one second, FEV_1_). Each scored on a 7-point scale from 0 (“no impairment”) to 6 (“maximum impairment”), and the overall score is calculated as the mean of all items, with lower scores indicating better control. Consistent with established guidelines, an ACQ score ≤0.75 will be used to identify “well-controlled asthma,” whereas a score ≥1.50 will indicate “poorly controlled asthma,” with intermediate values reflecting partially controlled asthma [41,42].

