The primary analyses will follow the intention-to-treat (ITT) principle, including all randomized households analyzed according to their assigned intervention group, to evaluate the effects of ERVs and portable HEPA air cleaners on IAQ, mold reduction, and asthma-related health outcomes by comparing the intervention and control (sham) groups using repeated measures analysis of variance (ANOVA) with a within-between interaction. Pairwise comparisons will be conducted between each intervention and control group (Group 1 vs. Group 2, Group 3 vs. Group 4) and between intervention groups (Group 1 vs. Group 3), using Tukey’s Honest Significant Difference (HSD) test to adjust for multiple comparisons. Repeated monthly ACT scores will be analyzed using multivariate mixed-effects models to account for within-subject correlations over time. Per-protocol (PP) analyses will be conducted as sensitivity analyses and will include only households that adequately adhered to the assigned intervention protocol. Intervention adherence will be assessed using plug load logger data for both ERV and air cleaner units, including device operation status and operating duration [52]. Additionally, subgroup analyses will be conducted to explore whether intervention effects differ by demographic and socioeconomic characteristics, baseline asthma severity, and baseline IAQ.

For secondary analyses, multivariate linear and logistic regression models will examine associations among housing characteristics, occupant behaviors, indoor environmental exposures (e.g., air pollutants and mold), and asthma-related health outcomes. Housing characteristics will be considered as potential covariates or confounders, when applicable, based on biological plausibility and statistical considerations. Prior to multivariable modeling, correlations among environmental exposure variables (e.g., PM, NO_2_, VOCs, and mold indices) will be evaluated using Pearson or Spearman correlation coefficients, depending on data distribution. Variance inflation factors (VIFs) will also be calculated to assess multicollinearity among predictors. Highly correlated exposures will not be included simultaneously in the same model to minimize multicollinearity, overfitting, and unstable estimates.

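### The ERV-versus-air-cleaner test (Group 1 vs Group 3) is not blinded to device type, so on self-reported outcomes it mixes efficacy with device-specific expectation; a net-of-sham contrast is needed

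*Protocol article*

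**What the plan says.** All references are to the protocol article.

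- **Hypothesis.** Under Objectives and hypotheses, the trial expects that the "two interventions will differ in both the profiles and magnitudes of IAQ and health improvements". The device comparison therefore covers health as well as air quality, and it belongs to the primary objective.
- **Contrast.** The Data management and statistical analysis plan section lists three pairwise comparisons under Tukey's HSD: Group 1 vs 2, Group 3 vs 4, and a comparison "between intervention groups (Group 1 vs. Group 3"). No listed contrast subtracts each device's sham response before comparing the devices.
- **Blinding.** The Interventions section states: "All participants will remain blinded to whether they receive the active or sham intervention throughout the entire study duration". It makes no claim about masking device type.
- **Shams.** For the ERV: "Sham ERVs will be installed in the same manner as active units but will be programmed to operate in recirculation mode". For the air cleaner: "Both active and sham air cleaner units will be sealed and have identical external appearance and installation configurations to maintain participant blinding". The air cleaner is "primarily placed in the living room (or in the bedroom if occupants spend the majority of their time").
- **Outcome.** For the primary asthma-control measure: "Monthly ACT surveys will be administered electronically using an online survey link distributed to participants". The ACQ adds symptom items and a lung-function item. Quality of life, stress and sleep are also questionnaires.

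**The concern.** A sham blinds a comparison only when the two arms compared look alike to the participant. That is true of active and sham ERV, and of active and sham air cleaner. It is not true of an active ERV and an active air cleaner: one is installed in the house by a contractor, the other stands in the living room or bedroom. If households expect more from one kind of device, or if the installation itself changes how they feel or report, self-reported scores can differ between Groups 1 and 3 with no difference in what the devices do to asthma.

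Neither safeguard in the plan deals with this. The within-between interaction removes baseline differences, but not an expectation that starts when the device arrives. Tukey's HSD controls multiplicity, not bias.

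At stake is the trial's comparative health claim. The plan explains the expected device difference by mechanism (particles, gases, humidity), yet Group 1 vs Group 3 on the ACT cannot separate mechanism from expectation. The two sham arms that could do so are already in the trial.

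**Working it through.** **1. Which listed contrasts are blinded**

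| Contrast | Do participants know which side they are on? | Open to expectation on self-report? |
|---|---|---|
| Group 1 vs 2 (ERV, active vs sham) | Masked by the recirculating sham | No, if blinding holds |
| Group 3 vs 4 (air cleaner, active vs sham) | Masked by the sealed, filterless sham | No, if blinding holds |
| Group 1 vs 3 (active ERV vs active air cleaner) | Device type is visible | Yes |

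That households know their device type is an inference. No sentence says so, but it follows from the descriptions of the devices.

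**2. The plan's own figure**

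Table 1 gives power 0.82 for the ACT with 24 measurements, f = 0.10 and total N = 76. The inputs not stated are assumed: correlation 0.5 and sphericity.

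- Noncentrality = f²·N·m/(1 − ρ) = 0.01 × 76 × 24 / 0.5 = 36.48
- Degrees of freedom = 3 × 23 = 69 and 72 × 23 = 1656
- Power = 0.815, which agrees with 0.82

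This figure concerns the overall interaction and says nothing about bias in one contrast. It does show that a correlation of 0.5 is consistent with the plan's table, so it is used below.

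**3. Size of the possible error (illustration)**

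Inputs from the article: 40 ERV and 40 air-cleaner homes, and monthly ACT. Assumptions: an equal active/sham split (20 per arm), 12 scores before and 12 after, correlation 0.5, no true device difference, and an expectation difference *b* of 0.1, 0.2 or 0.3 SD of a single score. *s* is the assumed SD of true change between people, in the same units.

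- Variance of one person's before-after change = (1 − 0.5)(1/12 + 1/12) + s² = 0.0833 + s²
- SE of Group 1 vs 3 = √[(0.0833 + s²) × 2/20]
- Tukey critical value, four groups and 76 df: about 2.63 on the t scale
- False-positive rate = P(|Z + b/SE| > 2.63)

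| s | SE | b = 0.1 | b = 0.2 | b = 0.3 |
|---|---|---|---|---|
| 0 | 0.091 | 6% | 33% | 74% |
| 0.3 | 0.132 | 3% | 13% | 36% |
| 0.5 | 0.183 | 2% | 6% | 16% |

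Without bias, this single comparison rejects in 0.9% of trials at 2.63, which is the reference for every cell.

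**4. The net-of-sham contrast**

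Let (Group 1 − Group 2) − (Group 3 − Group 4) be the contrast of changes. If *b* is the same in the active and sham arm of a device, it cancels. The variance involves four arm means instead of two, so the SE is √2 = 1.41 times larger. A difference that Group 1 vs 3 detects with 80% power corresponds to 1.96 + 0.84 = 2.80 SEs. Net of sham this is 2.80/1.414 = 1.98 SEs, and power is Φ(1.98 − 1.96), about 51% (both without multiplicity adjustment).

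**5. Would a same-direction check be enough?**

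One could keep Group 1 vs 3 as the test and ask only that the net contrast have the same sign. The two share the data of Groups 1 and 3 and correlate at 1/√2 = 0.71. In simulation with s = 0 and critical value 2.63, the share of false claims that passed the check was 97%, 84% and 63% for b = 0.1, 0.2 and 0.3. The check removes little, so the claim has to rest on the net contrast's own interval.

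**The case against.** The strongest case against runs as follows.

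- **Active versus active is a legitimate estimand.** The abstract speaks of effectiveness, and installation, noise and air mixing come with the device. This stands, and is why Group 1 vs 3 should be kept. But the hypothesis is argued from mechanism, and this contrast alone cannot support a mechanistic claim on self-report.
- **The shams are used.** Groups 1 vs 2 and 3 vs 4 are planned, and their difference is the net-of-sham estimate. That is correct as arithmetic, but two separate tests do not test whether the two effects differ.
- **An extra contrast can be left to the SAP.** The SAP is not shown and may add one. Still, the article itself lists the pairwise comparisons and fixes this one as the between-device test.
- **Size and direction are assumed.** This stands in full. Nothing in the article shows that expectation differs by device, and it may fade over 12 months. Ignoring Tukey's adjustment and variation in true change would give 20%, 59% and 91% for 0.1, 0.2 and 0.3 SD, which overstates the problem under the plan as written.
- **The shams may not be inert.** A recirculating ERV and a filterless fan both move air, and blinding may succeed better for one device than the other. This stands as a limit on the remedy.

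A reader might also infer that the article contradicts its own blinding claim, or that the trial as a whole is unblinded. Neither is supported. The claim covers active versus sham only, and both sham-controlled comparisons keep their masking.

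**Conclusion.** The point holds for one contrast and one class of outcomes. Group 1 vs Group 3 is unblinded to device type, and on the ACT/C-ACT, the ACQ symptom items, quality of life, stress and sleep it cannot separate efficacy from device-specific expectation and installation effects. The sham-controlled comparisons are unaffected. Measured air quality and mold are not open to reporting expectation.

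The size is unknown. Under the stated assumptions, false-positive rates run from about 2% (0.1 SD expectation difference, SD of true change 0.5) to 74% (0.3 SD, no variation in true change), against 0.9% without bias. The upper end is close to a worst case. It would be wrong to conclude that a Group 1 vs 3 difference must be an artefact, or that expectation favours the ERV; the article supports neither. What it does support is that such a difference on self-report would be ambiguous, and that arms already in the trial can reduce the ambiguity. The change should be made, but the trial does not fail without it.

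**What to change.** For self-reported outcomes:

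1. Prespecify the net-of-sham contrast (Group 1 − Group 2) − (Group 3 − Group 4), estimated from the same mixed model, and report it with its own confidence interval.
2. Rest any claim that one device has the larger sham-controlled effect on that interval, not on agreement in sign with Group 1 vs 3.
3. Treat it as a planned contrast outside Tukey's HSD, which covers pairwise differences only, and state the multiplicity rule that applies to it.
4. Keep Group 1 vs Group 3, labelled as the unblinded comparison of devices as delivered, and keep it for air quality and mold.

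The cost is one contrast from data already planned, with no new homes, visits or measurements. The article says that data collection had not begun and that the SAP is still to be finalised, so the change can be made before any data are seen. The price is precision: with an SE 1.41 times larger, a claim of device superiority becomes harder to reach. The contrast also rests on two assumptions that should be stated with the result: the shams are inert, and expectation depends on device type only.

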### Power calculations

The sample size and statistical power for this 4-arm parallel-group randomized controlled trial is analyzed for various scenarios based on a range of likely magnitudes of outcomes for asthma-related health outcome and environmental exposure assessments (Table 1). Calculations are made utilizing a robust statistical software tool, G*Power ver. 3.1.9.7, for a repeated measures ANOVA with a within-between interaction [49]. A range of effect sizes from small (Cohen’s f = 0.10), medium (f = 0.25), to large (f = 0.40) are considered to accommodate varying expected intervention effects, ensuring both robustness and generalizability of the findings [50]. Sample size calculations were conducted for the health outcomes (ACT and PFT) and environmental outcomes (IAQ and mold measurements). Required sample sizes were estimated based on expected effect sizes to achieve a statistical power >0.80 and adjusted for a 10% dropout rate. For monthly ACT surveys (n = 24) and monthly average low-cost IAQ measurements (n = 24), the required sample sizes ranged from 84 households for a small effect size (0.10) to 9 households for a large effect size (0.40). For PFT and mold measurements, the required sample sizes were estimated at 220 and 308 households, respectively, for detecting a small effect size (0.10); 40 and 53 households, respectively, for a medium effect size (0.25); and 18 and 26 households, respectively, for a large effect size (0.40). Although larger sample sizes were required to detect a small effect size (0.1) for PFT and mold, these estimates represent the sample sizes needed to detect very small changes. Further, the AIRVAC study was primarily designed to evaluate intervention effects on asthma outcomes and IAQ, for which the estimated sample sizes were within the planned recruitment range. Therefore, the final target sample size was set at 80 households, with an initial recruitment target of 88 households to account for potential dropout.

**Table 1 pone.0358221.t001:** Sample size calculations.

Effect Size (Cohen’s f for ANOVA)	Small			Medium			Large
	0.1	0.15	0.2	0.25	0.3	0.35	0.4

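### Tukey HSD protects six pairwise comparisons where three are planned; it is valid but costs about 7 to 11 points of power against Holm over the planned three

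*Protocol article*

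**What the plan says.** The section Data management and statistical analysis plan lists the pairwise comparisons as "Group 1 vs. Group 2, Group 3 vs. Group 4) and between intervention groups (Group 1 vs. Group 3" and assigns Tukey's "Honest Significant Difference (HSD) test to adjust for multiple comparisons". The sentence follows the description of the repeated measures ANOVA. The next sentence gives ACT its own model: "Repeated monthly ACT scores will be analyzed using multivariate mixed-effects models to account for within-subject correlations over time". It does not say whether the Tukey adjustment carries over to contrasts from that model.

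Under Primary outcome measures, two instruments follow the line "We will use the following measures to assess asthma control". Monthly ACT comes first, and ACQ is introduced with "In addition to monthly ACT, we will administer the ACQ during the home visits (V1-V4) to assess asthma control more comprehensively". The article does not rank them. Power calculations sizes the trial on ACT and PFT among the health outcomes, and does not name ACQ. The statistical analysis plan is still to be finalised and is not shown.

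**The concern.** With four arms there are six possible pairs, and Tukey sets its critical value so that the error over all six is 5%. Three of those pairs are not planned: active ERV against sham air cleaner, sham ERV against active air cleaner, and sham against sham. Protecting them raises the bar for the three comparisons that the trial is meant to answer and supports no planned claim in return. With a target of only 80 households, and a sample size set on an omnibus interaction test, there is no evident reserve for the loss.

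The choice also bears on the two asthma-control scores. Whatever error Tukey leaves unspent on one score is, in effect, available to the second. If only the group adjustment is changed, that cushion goes.

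**Working it through.** **Inputs from the article.** Four arms; three planned pairs; target 80 households, 40 per device type; four follow-up visits (two before and two after the intervention); 24 monthly ACT measurements; alpha 0.05 in Table 1.

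**Assumptions.** Equal split to 20 per arm; two-sided tests; one participant per household; correlation 0.5 between any two measurements; 12 ACT scores before and 12 after; both devices equally effective. Effect sizes are illustrative.

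**The plan's own figure.** For the ACT row of Table 1 at f = 0.10, N = 76, m = 24, k = 4:
- λ = f²·N·m/(1−ρ) = 0.01 × 76 × 24 / 0.5 = 36.48
- df1 = (k−1)(m−1) = 3 × 23 = 69; df2 = (N−k)(m−1) = 72 × 23 = 1656
- Power is 0.815, against 0.82 stated. It reproduces, so a correlation of 0.5 is consistent with the table. This is power for the omnibus interaction test, not for the pairwise contrasts.

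**Critical values (80 − 4 = 76 df).**
- Tukey: q(0.95; 4, 76)/√2 = 3.715/1.414 = 2.627, a per-comparison alpha of 0.0104
- Bonferroni on three: t(1 − 0.05/6; 76) = 2.448, alpha 0.0167
- Exact for these three contrasts, by simulation: 2.41, alpha 0.0183
- Holm steps: 2.448, then 2.287, then 1.992

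Because 2.627 exceeds every Holm step, any planned contrast that Tukey rejects Holm also rejects. Simulated family-wise error over the three planned contrasts under Tukey is 2.9%.

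**Power, one active-versus-sham contrast.** The contrast is the difference in mean change (after minus before). Its variance per household, in SD² units, is (1−ρ)(1/a + 1/b), with a and b the numbers of measurements before and after.
- Four visits: 0.5 × (1/2 + 1/2) = 0.5; SE = √(2 × 0.5/20) = 0.2236; noncentrality at 0.6 SD = 0.6/0.2236 = 2.68
- Monthly ACT: 0.5 × (1/12 + 1/12) = 0.0833; SE = √(2 × 0.0833/20) = 0.0913; noncentrality at 0.25 SD = 2.74

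| Outcome | Difference (SD) | Tukey | Holm | Loss |
|---|---|---|---|---|
| Four visits | 0.6 | 0.53 | 0.63 | 0.11 |
| Four visits | 0.7 | 0.69 | 0.79 | 0.10 |
| Four visits | 0.8 | 0.83 | 0.90 | 0.07 |
| Monthly ACT | 0.25 | 0.55 | 0.65 | 0.11 |
| Monthly ACT | 0.6 | >0.999 | >0.999 | none |

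Losses are taken before rounding. As a sample-size ratio at 80% power, Tukey against single-step Bonferroni on three is ((2.627 + 0.842)/(2.448 + 0.842))² = 1.11. Against the exact three-contrast value it is 1.14.

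**Error over ACT and ACQ together.** The article gives no correlation between the scores, so a range is shown. If Tukey is applied to both, the chance of any false rejection among the three planned contrasts on either score is 5.7% at correlation 0, 5.4% at 0.5, 5.1% at 0.7 and 4.3% at 0.9 (76 df; large-sample values run from 5.6% to 4.2%). If Holm is applied separately to each score with no ranking, it is 8.9% at correlation 0 and 6.6% at 0.9.

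**The case against.** The strongest reply is that Tukey is not wrong. Controlling the error over six pairs controls it over any three of them, and Tukey brings simultaneous confidence intervals, which Holm does not offer in simple form. That stands: nothing is contradictory here, and the matter is efficiency. It is also fair that the power loss vanishes for monthly ACT if the effect is 0.6 SD or more.

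A reader might go further and infer that two unranked primary scores inflate the error to between 8.4% and 9.7%. That needs a full 5% on each score, and the article nowhere says that each is tested that way; alpha 0.05 appears only in the sample-size note to Table 1. With Tukey on both scores the error stays near 5%. If the ACT mixed-model contrasts were left unadjusted, three tests at 5% would carry about 12.9%. The article is silent on that point, and silence does not establish it. A ranking of ACT and ACQ may also sit in the unseen analysis plan.

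Nor should this point be widened to homes that cannot take an ERV being assigned only to air-cleaner arms. That affects the comparability of Groups 1 and 3 under any multiplicity method and is a separate matter.

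**Conclusion.** The point holds as a low-cost improvement. Tukey HSD is valid but mismatched to the three planned comparisons: it uses about 2.9% of the available 5% and gives up about 7 to 11 points of power against Holm where power is moderate. The critical values rest on 20 households per arm. The power figures rest further on correlation 0.5, equal variances and equally effective devices, and no particular effect size is claimed as likely. The documents do not support a claim that the present plan inflates the error across ACT and ACQ. What they do show is that the near-5% error over the two scores is a by-product of Tukey's slack, so the group adjustment should not be changed without also settling the order of the scores.

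**What to change.** 1. Replace Tukey HSD by Holm over the three planned contrasts (1 vs 2, 3 vs 4, 1 vs 3): order the p-values and compare them with 0.05/3, 0.05/2 and 0.05, stopping at the first failure. State that the same rule applies to the group contrasts from the ACT mixed model.
2. Name monthly ACT, the asthma-control score listed first and used for sizing, as the primary measure, with ACQ tested after it. State the rule for passing to ACQ. Opening ACQ at the full 5% only once all three ACT contrasts are rejected is simple and holds the error; opening it on a single ACT rejection would not do so without splitting alpha.

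The cost is a few sentences, with no extra households or procedures. At the time of writing data collection had not begun and the analysis plan was not final. There are two downsides: ACQ loses equal standing, and Holm gives no simple simultaneous intervals. If such intervals are wanted, a single-step correction for the three contrasts (critical |t| 2.41 to 2.45) provides them and keeps much of the gain.

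### The per-protocol sensitivity analysis selects households on device use after randomisation without adjustment, and the scope for that selection may differ between ERV and air-cleaner arms

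*Protocol article*

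**What the plan says.** All points below are in the protocol article.

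- **Primary analysis** (Data management and statistical analysis plan): intention to treat, "including all randomized households analyzed according to their assigned intervention group", using repeated measures ANOVA with a within-between interaction. The pairwise contrasts are Groups 1 vs 2, 3 vs 4 and 1 vs 3.
- **Per-protocol analysis** (same section): "Per-protocol (PP) analyses will be conducted as sensitivity analyses". The set "will include only households that adequately adhered to the assigned intervention protocol". No adjustment for this selection is named.
- **Adherence data** (same section): "Intervention adherence will be assessed using plug load logger data for both ERV and air cleaner units, including device operation status and operating duration".
- **ERVs** (Interventions): "The ERV units will then operate continuously at the specified ventilation rate throughout the intervention period". In the paragraph on sham units: "Participants will not have access to the control panel settings during the study period".
- **Air cleaners** (Interventions): "Both active and sham air cleaner units will be sealed and have identical external appearance and installation configurations to maintain participant blinding". Sham units have their filters removed.
- **Checks at home visits** (Interventions): staff verify proper operation and blinding, "ensuring that ERV control panel settings remain unchanged and inaccessible to participants and that air cleaner unit seals remain intact".
- **Allocation** (Interventions): homes where an ERV cannot be installed may be assigned only to the air-cleaner arms.

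**The concern.** Device use is observed after randomisation. Keeping only households that used the device enough turns a randomised comparison into one between self-selected groups, unless the selection works alike in the arms compared or is unrelated to how the outcome changes. The descriptions of the devices give a reason to doubt that it works alike. For ERVs the text describes continuous running and a panel kept from participants. For air cleaners it describes a seal whose stated purpose is blinding, and the specific check listed is that the seal is intact. If occupants can switch air cleaners off, exclusions driven by behaviour would be more common in Groups 3 and 4.

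What is at stake is interpretation. If the per-protocol estimate is larger than the intention-to-treat estimate, it will be tempting to read the gap as the benefit of real use. It could instead reflect which households keep a device running. The comparison of the two devices is part of the primary objective, so a per-protocol Group 1 vs Group 3 result would attract attention.

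**Working it through.** The plan gives no figure for adherence or for the per-protocol effect, so there is none to reproduce. The check is in four steps.

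**1. When does the subset bias the planned contrast?** Let e be the fraction of an arm excluded, and let d be the mean pre-to-post change in retained homes minus that in excluded homes. Then

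retained mean change − all-household mean change = e × d,

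and the bias in a contrast between arms A and B is e_A × d_A − e_B × d_B. It is zero if adherence is unrelated to change (d = 0 in both arms), or if e × d is the same in both arms.

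**2. A stable gap in level does not count.** Suppose excluded homes score g points lower throughout. Dropping them raises the retained mean by e × g before the intervention and by e × g after it. The shift in change is e × g − e × g = 0. The within-between interaction compares changes, so such a gap cancels. Only a relation between adherence and *change* matters.

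**3. Illustration with a true effect of zero.** All inputs are assumptions: ERV adherence of about 95%, unrelated to behaviour; air-cleaner adherence of 62% to 81%, depending on a household trait; and that trait correlated 0.5 with the outcome. The simulation has one outcome per household (SD 1). It bears on the planned analysis only if that outcome is read as the pre-to-post change, in SD units of change.

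| Assumed adherence in active and sham air-cleaner homes | Adherent, Group 3 / Group 4 | Bias 1 vs 2 | Bias 3 vs 4 | Bias 1 vs 3 |
|---|---|---|---|---|
| (a) Same mechanism | 62% / 62% | 0.00 | 0.00 | −0.16 |
| (b) Less trait-driven in sham | 62% / 81% | 0.00 | +0.13 | −0.16 |
| (c) Trait acts in opposite directions | 62% / 64% | 0.00 | +0.24 | −0.15 |

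Check of (a) against step 1: the excluded fraction in Group 3 is 1 − 0.621 = 0.379 and the retained mean is 0.159. The overall mean is 0, so the excluded mean is −0.159 × 0.621 / 0.379 = −0.26. Hence d = 0.159 + 0.26 = 0.42 and e × d = 0.379 × 0.42 = 0.16, as simulated.

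**4. What an instrumental-variable estimate does.** Within an active-sham pair, let the exposure be active-device use, zero in sham. The estimate is the intention-to-treat difference divided by mean use in the active arm. If mean use were 0.62 of full use, the estimate and its standard error would both be multiplied by about 1/0.62 = 1.61 (treating mean use as known). Analysing only 62% of homes in each arm would multiply the standard error by about 1/√0.62 = 1.27. At mean use of 0.95 the instrumental-variable factor is 1/0.95 = 1.05, so for ERVs the result would nearly restate intention to treat.

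**The case against.** The strongest reply is that the article makes intention to treat primary, offers per-protocol only as a sensitivity analysis, and nowhere says that it estimates the effect of use. That stands, and it limits the point to a secondary result. A second reply is that the adherence cut-off may be in an analysis plan that is not shown. That also stands, but no cut-off removes selection on post-randomisation use.

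Several stronger readings are tempting, and the document does not support them.

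- A reader might infer that occupants can freely control the air cleaners. The article is silent. The units are sealed and it does not say what the seal covers.
- A reader might infer that nearly all ERV homes stay in the per-protocol set. ERV use is logged too, so ERV homes can also be excluded, and restricting the panel is not shown to prevent power being cut.
- A reader might infer that excluding homes with poorer asthma control creates a spurious effect. A stable difference in level cancels in the planned interaction (step 2).
- A reader might infer that the per-protocol result can never inform on use. In case (a), where blinded active and sham homes adhere alike, the 3 vs 4 bias is zero. That filter removal would change how units are used is possible but not documented.
- A reader might infer that an air cleaner left on its lowest setting counts as fully adherent. The article lists status and duration as included in the logger data and fixes no such rule.

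It can also be said that the proposed estimate is a rescaled intention-to-treat result under an added linearity assumption. That is true. Its merit is that it keeps the randomised comparison.

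**Conclusion.** The concern holds in a limited form. The per-protocol set is chosen on post-randomisation use with no adjustment named, so it is open to bias if adherence is related to change in outcome and that relation differs between arms. The unequal description of ERV and air-cleaner operation makes a difference by device type plausible, not established.

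No size follows from the document. Under the assumed inputs the bias is about 0.16 SD of change in Group 1 vs Group 3, and 0 to 0.24 SD in Group 3 vs Group 4. Both depend wholly on those inputs.

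Group 1 vs Group 3 is the most exposed. Adherence selection would be added to a comparison already limited by allocation, because homes not feasible for an ERV can enter only the air-cleaner arms. The article does not say whether the per-protocol analysis repeats this contrast. The primary intention-to-treat result is not affected by this point, which is an improvement to a sensitivity analysis and not a flaw in the main result.

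**What to change.** In the statistical analysis plan:

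1. Within each active-sham pair (1 vs 2 and 3 vs 4), specify an instrumental-variable (complier-average) estimate, either as the adherence analysis or beside the per-protocol subset. Assignment is the instrument, logged active-device use is the exposure (zero in sham), and all randomised households are kept.
2. State its assumptions: assignment affects the outcome only through active use, and the effect is linear in use. State that its interval will be wider than that of the per-protocol subset.
3. Do not interpret a per-protocol Group 1 vs Group 3 contrast as an effect of use.
4. Report logged use by arm, and state whether occupants can control the air cleaners.

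The cost is a few sentences and one further model on logger data already planned, plus the loss of precision shown above. The article says that data collection has not begun and that the analysis plan will be finalised before data lock and unblinding, so the change can still be prespecified.
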